Osteoarthritis progression involves subchondral bone alterations, which exercise may counteract by preserving cartilage and bone integrity [14,20]. Bone cartilage fragments (distal femur condyle and tibial plateau) will be collected post-osteotomy, stored in sterile tubes, and processed for mitochondrial activity assays and immunohistochemical analysis of extracellular matrix structure. Markers include fibronectin type III domain-containing 5 (FNDC5), β-galactosidase (senescence marker), Bcl-2-associated X protein (BAX), and cytochrome C (Cyt-C). These markers will provide insights into mitochondrial function, programmed cell death, and cartilage remodeling, helping evaluate the local physiological response to the exercise program. Mitochondrial membrane permeability will be assessed using flow cytometry (Mitochondrial Membrane Potential Kit, MAK160, Merck). Due to considerable inter-individual variability and limited evidence directly connecting these biomarkers to prehabilitation in OA, FNDC5/irisin and β-galactosidase levels should be interpreted as exploratory outcomes. Effect sizes are expected to be small to moderate. Nevertheless, FNDC5 has demonstrated chondroprotective mechanisms in OA models, including enhanced cartilage integrity and reduced chondrocyte apoptosis [24], supporting its inclusion to explore metabolic and cellular adaptations to exercise.

Self-reported pain, stiffness, knee function, and anthropometric measurement

The Western Ontario and McMaster Universities Arthritis Index (WOMAC), a validated tool for knee osteoarthritis and post-TKA patients, assesses pain (5 items, 0-20 points), stiffness (2 items, 0-8 points), and physical function (17 items, 0-68 points) [25]. The total score is obtained by summing the individual scores and can be converted to a 0-100 scale, with higher values indicating greater impairment. Body mass will be measured using the Líder® P150C digital scale (São Paulo, Brazil). Height will be assessed using a Ghrum Polar Manufacture Instruments® anthropometer (Geneva, Switzerland). Waist circumference will be measured with Sanny® anthropometric tape (São Paulo, Brazil). Both the WOMAC and the anthropometric measurements will be performed at three moments: multidisciplinary consultation, pre-hospitalization, and 30-day follow-up consultation.

Prehabilitation adherence

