Patient satisfaction will be assessed 30 days post-TKA using a validated TKA satisfaction questionnaire [27]. This time point was selected to capture the short-term functional and symptomatic benefits of prehabilitation when effects on recovery are most tangible. Four primary questions, rated on a five-point Likert scale, will evaluate pain relief, functional improvement, and overall satisfaction. Scores ranged from 0 (very dissatisfied) to 100 (very satisfied), with the total score calculated as the mean of all responses. The total satisfaction score will be obtained by summing the individual scores of the four satisfaction questions and dividing by four. If any individual component is missing, the total score will not be calculated.

Sample size

The sample size was estimated using repeated measures analysis of variance with four time points (nine weeks pre-TKA, one day pre-TKA, three days post-TKA, and 30 days post-TKA) and two groups (experimental and control). Assuming a moderate effect size (f = 0.25), α = 0.05, and 80% power (β = 0.20), 78 participants were required (G*Power 3.1.9.7, University of Kiel, Germany). This effect size was selected based on evidence from a study in TKA patients with CRP as the primary outcome, which reported a between-group difference of 9.12 mg/L and a pooled standard deviation of 10.95, corresponding to a Cohen’s d of 0.83 (f ≈ 0.29), and statistical power of 88% with 61 participants. Therefore, f = 0.25 was adopted as a conservative and evidence-based estimate for the current trial [28]. Accounting for a 10% potential attrition rate, the final target sample size was 86 participants.

Blinding

This study follows a single-blind design, in which only the data analyst remains blinded to group allocation. Due to the nature of the intervention (an exercise program), blinding participants or intervention providers was not feasible, as doing so would compromise adherence, safety, and protocol fidelity. Consequently, participants, data collectors, and outcome assessors will be aware of group assignments.

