We recognized potential challenges related to adherence and digital proficiency within our target age population (50-75 years). Cognitive impairments may also influence participation. However, we anticipate that video-based interactions will enhance motivation, accountability, and social support by closely replicating in-person coaching. Evidence suggests that frequent participant contact via telephone, Internet, or personal visits improves adherence to home-based exercise programs among older adults [33]. Telecommunication difficulties between participants and researchers are expected; however, to mitigate these issues, we will provide clear instructions for video call setup and allocate sufficient time to address technical challenges within our study schedule. We anticipate that technical barriers will be most prominent at the beginning of the program and diminish as participants become more accustomed to the process. Notably, a recent Brazilian study demonstrated that WhatsApp-based audio and visual messaging was effective in delivering a six-week psychosocial intervention to older adults, even without direct support from health professionals [34].

Another methodological limitation is the single-blind design, which may introduce performance and detection bias, particularly in subjective outcomes. To mitigate these biases, all outcome assessments will follow standardized protocols and be conducted by the same team of trained evaluators across both groups. Furthermore, participants in both arms will receive uniform instructions regarding their routine daily activities between baseline and surgery, minimizing behavioral discrepancies apart from the intervention itself. While self-reported outcomes are inherently prone to bias, they are measured using validated instruments with low response bias. In addition, we will perform sensitivity analyses to explore the robustness of results by accounting for potential confounders such as adherence, engagement levels, and expectancy effects. Importantly, the trial also includes objective outcomes, such as biomarkers, length of stay, complications, and anthropometric data, which enhance the overall internal validity of the findings despite the inherent limitations of a non-blinded behavioral intervention.

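### Laboratory and tissue readers are left aware of allocation for a reason that applies only to participants and exercise providers; coded samples would remove avoidable detection bias in the judgement-dependent readings

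*Protocol article*

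**What the plan says.** The Blinding section (Materials and methods) opens: "This study follows a single-blind design, in which only the data analyst remains blinded to group allocation". It gives one reason, the nature of the exercise intervention: "blinding participants or intervention providers was not feasible, as doing so would compromise adherence, safety, and protocol fidelity". It then concludes that, in consequence, "participants, data collectors, and outcome assessors will be aware of group assignments".

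Strengths and limitations (Discussion) returns to the subject: "Another methodological limitation is the single-blind design, which may introduce performance and detection bias, particularly in subjective outcomes". As a safeguard it says that "all outcome assessments will follow standardized protocols and be conducted by the same team of trained evaluators across both groups". It adds uniform instructions on daily activity, validated questionnaires, and sensitivity analyses for adherence, engagement and expectancy. It closes the argument by noting that "the trial also includes objective outcomes, such as biomarkers, length of stay, complications, and anthropometric data", and says that these strengthen internal validity.

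The outcome sections show where the readings are made. Part of each blood sample is frozen as plasma for later IGF-1, IL-1β and IL-6 measurement. Synovial supernatant is frozen and analysed later. Bone-cartilage fragments are placed in tubes and "processed for mitochondrial activity assays and immunohistochemical analysis of extracellular matrix structure". Length of stay, readmissions and complications come from the medical record, and complications are classified by Clavien-Dindo.

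**The concern.** The step from the reason to the conclusion does not hold. Adherence, safety and fidelity explain why a participant or an exercise provider must know the arm. They do not explain why a person scoring a stained section or setting a cytometry gate must know it. The text nevertheless presents the unblinding of assessors as a consequence of the intervention.

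Knowledge of the arm could move a judgement-dependent reading towards the hypothesis that prehabilitation helps. A blinded analyst cannot undo this, because the bias would already be in the recorded value. The synovial and tissue markers and the complications are compared between arms as secondary outcomes (statistical methods, under Results). For FNDC5/irisin and β-galactosidase the protocol itself expects wide variation between individuals and effects no larger than moderate, so a modest reader effect could be hard to tell from a treatment effect.

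**Working it through.** No figure in the plan depends on this point, so there is no arithmetic to reproduce. Masking assessors would change neither the 78 required nor the 86 targeted participants. The check sets the blinding text against how each outcome is obtained.

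**Step 1: who is covered by the stated reason.** Participants and intervention providers only. No separate reason is given for data collectors or outcome assessors.

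**Step 2: where each outcome is read, and how much judgement it can involve.** The judgement column is an assessment; the protocol does not describe reading rules.

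| Outcome (section) | Where or how it is obtained | Can the reader be masked by a sample code? | Room for judgement |
|---|---|---|---|
| CRP (Primary outcome) | Blood sample, laboratory assay | Yes | Small, assuming an instrument-read assay |
| Other blood markers (Additional blood biomarkers) | Part assayed at once, part frozen | Yes | Small where instrument-quantified |
| Synovial cytokines, free DNA (Synovial fluid biomarkers) | Frozen supernatant; bead-array kit, fluorescent probe | Yes | Small for kit quantification; some if gates are set by hand |
| Immunohistochemistry (Tissue biomarkers) | Tissue after osteotomy | Yes | Largest |
| Mitochondrial membrane assay (Tissue biomarkers) | Flow cytometry with a kit | Yes | Some, through gating |
| Clavien-Dindo grade (Hospital outcomes) | Medical record | No; needs a grader unaware of allocation | Some |
| Length of stay (Hospital outcomes) | Count of days from the record | No | Little in abstraction; discharge decisions are a separate matter |
| Anthropometry | Face to face | No | Some; not changed by coding |
| WOMAC, satisfaction | Participant's own report | No | Participant is unblinded in any case |

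**Step 3: does another section supply masking?** No. No section mentions coded samples, masked readers or masked grading.

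**Step 4: do the listed safeguards substitute for it?** Standard procedures and a single evaluator team make readings consistent, but a team that knows the arm can be consistently wrong in one direction. The sensitivity analyses concern participant behaviour and expectation, not reader knowledge. The blinded analyst acts after the values are fixed.

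**Result.** For the blood, synovial and tissue rows the unblinding is a choice, not a consequence of the intervention. The exposure is concentrated in immunohistochemistry and cytometry gating. Clavien-Dindo grading is also exposed but needs a different remedy.

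**The case against.** Four arguments on the other side deserve weight.

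- **The primary outcome is barely touched.** This stands. With an instrument-read CRP assay, knowing the arm leaves little room to alter the result. A reader might infer that the trial's main conclusion is compromised, or that everything listed as objective is biased. The document supports neither. Length of stay is a count, kit-quantified assays leave little discretion, and some tissue markers are already labelled exploratory.
- **An article may omit laboratory practice.** This stands in part. Labelling and batching are operational details that a full protocol may hold, and the article does not show that tubes or slides carry the allocation. A reader might infer that they do; that is not established. But the article does not merely stay silent. It says the analyst alone is masked and that outcome assessors know the arm. If laboratory staff are in fact masked, that statement is wrong and still needs correcting.
- **The limitation is disclosed.** True, and the objective outcomes are one of several safeguards offered, so it would go too far to say that the trial loses its main defence. An assay result also remains less open to expectation than self-report. Disclosure does not, however, justify keeping a bias that can be avoided.
- **Masking is not free.** This stands for complication grading. It may need one person to prepare the record and another, unaware of allocation, to grade it, and Trial design ties the pace of recruitment to staffing. It does not stand for sample coding, which needs no new visit, sample or assay. Nor would a masked grader mask ward staff, who may learn the arm from participants and who decide discharge and write the record.

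**Conclusion.** The point holds in a limited form. The Blinding section states that all data collectors and outcome assessors know the allocation, and its reason does not apply to people who read samples away from the participant. The resulting detection bias is avoidable for blood, synovial and tissue read-outs.

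Its size cannot be derived from the document. It is probably small for CRP, other instrument-quantified assays and length of stay, and of more concern for immunohistochemistry and cytometry gating, with Clavien-Dindo grading also open to it. This ranking assumes that CRP is read by an instrument and that staining and gating involve some reader discretion; the article states neither. The sample-coding change is worth making because it is inexpensive and protects secondary outcomes that the article cites in support of internal validity. It is not a threat to the primary analysis.

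**What to change.** Replace the last sentence of the Blinding section with text to this effect:

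> Blood, synovial and tissue samples carry a study code that does not reveal allocation. Laboratory staff, tissue readers and flow-cytometry operators are blinded, and samples from both arms are mixed within each assay batch. Participants, exercise providers, face-to-face data collectors and clinical staff who may learn the arm are not blinded.

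The opening sentence of that section, which names the analyst as the only blinded role, must change with it.

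For complications, have an existing team member who is unaware of allocation assign the Clavien-Dindo grade, if there is one. Otherwise, report complication grading as unblinded.

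In Strengths and limitations, say which outcomes are masked and which are not: WOMAC, satisfaction, anthropometry and discharge decisions (and through them length of stay) remain unblinded.

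The cost is minor sample-handling work: coded labels and planned batches. No visit, sample, assay or sample-size figure changes. The article gives no cost figure, so calling this minor is a judgement. Coding has to be in place before samples are read, because a value read with the arm known cannot be made blind afterwards.

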## Results

The significance level was set at p < 0.05, and analyses will be performed using IBM SPSS Statistics 21.0 (IBM®, Armonk, NY, USA). Data normality will be assessed using the Shapiro-Wilk test. Baseline demographic characteristics will be compared between the groups using independent t-tests (normal data), Mann-Whitney U tests (non-normal data), and chi-square or Fisher’s exact tests (categorical variables).

The primary outcome, changes in plasma CRP levels across four time points (nine weeks pre-TKA, one day pre-TKA, three days post-TKA, and 30 days post-TKA), and WOMAC scores across three time points (baseline, one day pre-TKA, and 30 days post-TKA) will be analyzed using two-way repeated-measures ANOVA (group × time interaction), contingent upon assumptions of normality and sphericity. If these assumptions are violated, linear mixed models (LMM) or generalized estimating equations (GEE) will be employed as more robust alternatives, capable of handling missing data and irregular intervals. Post-hoc pairwise comparisons will use the Bonferroni correction to adjust for type I errors. For non-parametric repeated measures, the Friedman test will be used, followed by Dunn-Bonferroni post-hoc tests when applicable.

Secondary outcomes, including synovial fluid and tissue biomarkers, hospital outcomes (length of stay, complications, readmissions), and satisfaction scores at specific time points, will be compared between groups using independent t-tests (normal data) or Mann-Whitney U tests (non-normal data). Correlations between biomarkers, hospital outcomes, WOMAC scores, and satisfaction will be examined using repeated measures correlation (rmcorr) for normal data or generalized linear mixed model (GLMM) for non-normal data. Rmcorr will be applied when assessing the strength and direction of associations between two continuous variables measured repeatedly within individuals. GLMM will be used in cases requiring the modeling of random effects, adjustment for covariates, or handling of non-normal or categorical outcomes, ensuring analytic flexibility across diverse data structures. To account for multiple comparisons in biomarker and exploratory analyses, false discovery rate (FDR) adjustment will be applied where appropriate.

Effect sizes (e.g., partial eta-squared for ANOVA and Cohen’s d for pairwise tests) and 95% confidence intervals will be reported alongside p-values to enhance the clinical interpretability of findings.

Missing data will be addressed using linear regression models to examine the dose-response relationship, including participants who did not reach the ≥75% adherence threshold as well as those who withdrew from the intervention due to comorbidities or frailty. These individuals will be retained in the analysis to reflect real-world variability.

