In TKA, the extent of surgical trauma significantly influences postoperative pain and recovery. Plasma CRP, a well-established biomarker of tissue injury and inflammation, is commonly used to monitor recovery due to its rapid response, high specificity for acute inflammation, and ease of measurement, especially in elderly arthroplasty patients. CRP was selected as the primary outcome because of its association with osteoarthritis severity, surgical response, and postoperative complications, typically peaking on the third postoperative day [17].

Blood samples will be collected in an outpatient setting at four periods: before and after the eight-week prehabilitation program and three and 30 days post-TKA in both the experimental and control groups. The preoperative measurement one day before surgery (t3 in Figure 1) was timed to reflect chronic systemic adaptations resulting from prehabilitation while minimizing the confounding influence of acute exercise responses. This decision is supported by evidence showing that CRP typically returns to baseline (or a new post-exercise baseline) within six days after cessation of exercise [18]. The third postoperative day (t5) was selected to capture the peak inflammatory response following surgery, as supported by TKA-specific literature [17]. This time point also coincides with the typical hospitalization period, facilitating consistent, in-hospital sample collection. In the long term, given the anti-inflammatory effects of physical exercise, sustained reductions in CRP levels may reflect the effectiveness of the intervention in modulating systemic inflammation and promoting recovery [14].

Given that CRP levels can be influenced by factors such as sleep deprivation and acute infections, additional control measures will be implemented. Participants will report their average sleep duration and quality during the week preceding each blood draw (except for the third-day post-TKA measurement), as insufficient or disturbed sleep is associated with elevated CRP levels. Additionally, clinical symptoms suggestive of viral or bacterial infections (e.g., fever, sore throat, cough, or malaise) will be assessed before each collection since such conditions may increase CRP levels and confound the interpretation of the intervention's effects [19]. These precautions aimed to strengthen the internal validity of CRP as a primary outcome by minimizing interference from unrelated acute inflammatory processes.

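### The primary CRP test is a 3-df group × time interaction with baseline as an outcome level, no baseline covariate and no primary contrast, so it shows neither direction nor timing and is inefficient for a sustained effect

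*Protocol article*

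**What the plan says.** The statistical text stands under the Results heading of the protocol article. The primary outcome is "changes in plasma CRP levels across four time points (nine weeks pre-TKA, one day pre-TKA, three days post-TKA, and 30 days post-TKA"), and these values "will be analyzed using two-way repeated-measures ANOVA (group × time interaction), contingent upon assumptions of normality and sphericity". WOMAC gets the same treatment over three times. If the assumptions fail, "linear mixed models (LMM) or generalized estimating equations (GEE) will be employed as more robust alternatives"; no baseline covariate is mentioned there either. Adjustment for covariates appears only in the correlation analyses: "GLMM will be used in cases requiring the modeling of random effects, adjustment for covariates". Follow-up is by post hoc tests: "Post-hoc pairwise comparisons will use the Bonferroni correction to adjust for type I errors".

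The Randomization subsection places randomisation after the baseline assessments. The Primary outcome subsection gives reasons for more than one sample. Of day 3 it says "The third postoperative day (t5) was selected to capture the peak inflammatory response following surgery"; the sample one day before surgery is justified as reflecting chronic adaptation to the programme; and lasting reductions are described as a possible sign of effectiveness. None of these is ranked above the others.

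**The concern.** Baseline CRP is taken before allocation, so the arms can differ there only by chance. The planned test does not use that knowledge. It asks whether the between-arm difference is the same at all four times, and it treats the baseline difference as unknown, like the other three.

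Two things follow. First, the test responds to any departure from parallel profiles, including benefit at one time and harm at another. Rejection does not answer the trial's directional hypothesis; that is left to post hoc pairs. Second, if prehabilitation lowers CRP by a similar amount at all three later times, the interaction detects this only through the contrast with one noisy baseline value, and the part of the effect that shows as an average difference between arms is discarded. At stake are a primary result that is hard to interpret and some loss of power, of a size that depends on quantities the protocol does not give.

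**Working it through.** **Inputs from the protocol.** Two arms, 1:1, four times; 78 participants before attrition, so 39 per arm expected; two-sided α = 0.05; the source study's d = 0.83.

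**Assumptions, not in the protocol.** Correlation ρ between CRP values, 0.3/0.5/0.7 (0 and 0.1 also tried); equal SDs and compound symmetry, except in step 5; effect 0.5 SD.

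**The plan's own figure.** The article obtains 78 from a repeated-measures ANOVA with f = 0.25. It does not state the correlation or which effect was powered. The interaction at f = 0.25 needs 46 participants at ρ = 0 and 24 at ρ = 0.5; the between-groups main effect needs 82 at ρ = 0.5. So 78 does not follow from the stated inputs alone. That is a separate matter; 78 is taken as given here.

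**Step 1: planned interaction.** Numerator df = (2−1)(4−1) = 3, denominator df = 3 × (78−2) = 228. With δ the vector of arm differences over the four times (0 at baseline), λ = (N/4) × Σ(δ − mean δ)² / (1−ρ).

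- 0.5 SD at day 3 only: Σ = 0.25 × 3/4 = 0.1875, so λ = 19.5 × 0.1875/(1−ρ) = 5.22/7.31/12.19. Power 45/60/84%.
- 0.5 SD at all three later times: Σ is again 0.1875, so λ and power are identical.

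**Step 2: no direction in the result.** A benefit of 0.25, 0.5 and 0.25 SD at the later times gives Σ = 0.125. A benefit of 0.25 SD before surgery, harm of 0.25 SD at day 3 and nothing at day 30 also gives Σ = 0.125. Both have power 31/42/65%. The test cannot tell them apart.

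**Step 3: same 3-df question, baseline as covariate.** The three later values have residual covariance (1−ρ)I + (ρ−ρ²)J, and λ = (N/4) δ′S⁻¹δ with 3 and 73 df.

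- Day 3 only: λ = 19.5 × 0.25(1+2ρ)/[(1+3ρ)(1−ρ)] = 5.86/7.80/12.58.
- All later times: λ = 19.5 × 0.75/[(1+3ρ)(1−ρ)] = 11.00/11.70/15.73.

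| Power at ρ = 0.3/0.5/0.7 | Planned interaction | Baseline-adjusted 3-df test |
|---|---|---|
| 0.5 SD at day 3 only | 45/60/84% | 49/62/84% |
| 0.5 SD at all later times | 45/60/84% | 78/81/92% |

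**Step 4: naming one time as well.** For a day-3 effect, an unadjusted day-3 t test has 58.7% power and the baseline-adjusted contrast 63/71/86%. At ρ = 0.3 the step from 45.1% to 62.7% is 17.6 points: 13.6 from choosing the time (45.1 to 58.7) and 4.0 from adjustment (58.7 to 62.7). If the effect is before surgery only, the day-3 contrast has 5% power and the planned interaction keeps 45/60/84%.

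**Step 5: unequal variances.** With assumed SDs 5, 5, 40, 10 and 0.5 SD at day 3 only (4,000 simulated trials per setting), the Greenhouse–Geisser interaction has 60/63/64% power at ρ = 0.1/0.3/0.5 and the adjusted day-3 contrast 59/63/69%: a gain of −1 to about +4 points. The uncorrected interaction F has a type I error of about 9–10% there, although the plan makes the ANOVA conditional on sphericity.

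**The case against.** The group × time test is valid under randomisation. A baseline kept among the outcomes is not itself an error, since constrained-baseline mixed models do this too. The plan has a mixed-model or GEE fallback, and its Bonferroni pairs, effect sizes and 95% confidence intervals would help to locate an effect. All of this stands. But the fallback carries no baseline term, and the pairs are post hoc with none marked as primary.

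Three stronger readings are tempting, and the document supports none of them.

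- A reader might infer that baseline adjustment recovers lost power at no cost. Steps 3 and 4 show that, for a day-3-only effect, adjustment alone adds about 0 to 3 points to the 3-df test at ρ from 0.3 to 0.7. Most of a larger gain at low correlation comes from choosing the time, and that choice can miss an effect elsewhere.
- A reader might infer that day 3 is the protocol's intended primary time. The Primary outcome subsection also justifies the sample one day before surgery, and the Discussion treats both periods as critical.
- A reader might infer that the trial is underpowered. At the source effect of d = 0.83, at day 3 only or equal at all later times, the planned interaction has 80/90/97/99.9% power at ρ = 0.1/0.3/0.5/0.7 (76% at ρ = 0).

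**Conclusion.** The point holds as one of interpretation and efficiency, not of validity. The protocol fixes a 3-df omnibus test with a pre-randomisation value among its outcome levels, gives no baseline covariate in either the main or the fallback analysis, and names no primary contrast. That rejection shows neither direction nor timing follows from the form of the test and needs no assumption about correlation.

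The size of the power loss does need assumptions. With equal SDs, compound symmetry, 39 per arm, 0.5 SD and ρ from 0.3 to 0.7, it is about 8 to 33 points for an effect equal at all later times (84.0 to 91.5% at ρ = 0.7; 45.1 to 78.0% at ρ = 0.3) and about 0 to 3 points for an effect at day 3 only. It may be close to nil where day-3 variance dominates, which is plausible for a marker that peaks on that day. The change is worth making, but no single figure for recovered power should be quoted.

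**What to change.** Analyse the three post-randomisation CRP values, on the log scale if skewed, in a mixed model with arm, time, arm × time and baseline CRP as covariate; a constrained-baseline model is an equivalent choice. Report the adjusted between-arm difference with its 95% CI at one day pre-TKA, day 3 and day 30. Use the same structure for WOMAC with its two later times.

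Before unblinding, the sponsor should state which adjusted contrast is primary and make the others secondary. The protocol's own reasoning supports either day 3 or one day pre-TKA, so the choice is the sponsor's.

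The cost is wording only, because every value needed is already scheduled for collection. The adjustment carries little downside. Committing to one contrast does carry one: it narrows the primary question and gives little chance of a positive primary result if the effect occurs only at another time.
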